### PROBE design

Clinical outcome assessments at 90 days will be performed by independent adjudicators (experienced stroke neurologists) who are not directly involved in the patient’s treatment and who are blinded to treatment assignment.

To ensure adequate blinding of outcome assessors, the following measures will be implemented: (i) assessors will have no access to treatment allocation information in medical records or study documentation; (ii) a site coordinator not involved in outcome assessment will accompany the patient and ensure no treatment-related discussions occur; and (iii) assessor blinding will be verified and documented after each assessment using a standardized questionnaire to evaluate potential unblinding.

A radiologist blinded to the treatment allocation will centrally adjudicate the baseline brain NCCT and CTA scan on Day 1 and the follow-up CT scan on Day 2 and a delayed follow-up CT scan on Day 14.

### Primary objectives

Safety outcome: mortality at day 90.Efficacy outcome: regaining functional independence (mRS 0–2) at Day 90 following stroke onset.

### Secondary objectives

Neurological improvement from the deficit at baseline measured by NIHSS at Day 2, 7, 30, and 90.Ordinal shift analysis of mRS at Day 90.Improvement in activities of daily living from the status at baseline measured by BartheI Index on Day 30 and 90.Avoiding hematoma growth from Day 1 to Day 2, defined as both absolute (>12.5 mL) and relative (>35%) increases in hematoma volume measured using semi-automated volumetric analysis on NCCT.Absolute hematoma size shift.SAE until day 30.

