To date no approved medicine mitigates the neurological and functional effects of hemorrhagic stroke. There is limited innovation in the development of novel neuroprotective therapeutics for ICH. Results from ischemic stroke trials provide a good rationale for investigating cerebrolysin in a well-designed randomized trial for the hyperacute ICH. One single study on an animal model of hemorrhagic stroke showed that administration of cerebrolysin results in reduced mortality and improved neurological outcome (36).

The observational retrospective study from 2019 that evaluated cerebrolysin treatment in patients with a minimally conscious state (MCS) observed a statistically significant improvement in the level of consciousness regardless the type of stroke (ischemic, hemorrhagic) (37).

Two trials have previously assessed cerebrolysin’s efficacy and safety in ICH. The first one demonstrating no effect after a 10-day treatment course. From the current perspective, those results must be reassessed due to several methodological limitations and advances in stroke care standards. The trial was conducted at a single center and enrolled patients with basal ganglia hematomas in whom neuroprotective and neuroregenerative effects are inherently challenging to demonstrate. The outcome measures were non-standard compared to those used generally for reporting stroke outcomes. Long-term outcomes were not reported, and the intervention did not involve early intensive rehabilitation (important for benefit from the synergistic effect of cerebrolysin and rehabilitation) and was initiated in a 6- to 24-h time window (38). This could also have affected the neutral outcome, as hematoma growth occurs mainly within 6 h of symptom onset (39). Another recent study showed a positive effect of cerebrolysion on functional outcome measured on the modified Rankin Scale (mRS) and Barthel Index and also reduced 6-month mortality (40) dose used in these patients was 30 mL daily over 21 days. Time from onset to needle was predefined as 12 h, nevertheless the patients were treated beyond 13 h of onset and less than 40% experienced lobar ICH.

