### Intervention

The selected cerebrolysin dosage of 50 mL daily for 14 consecutive days is based on several considerations: (i) efficacy data from previous ischemic stroke trials suggesting that higher doses (30–50 mL) may produce more robust effects than lower doses; (ii) safety profile established in previous clinical studies confirming tolerability of this dosing regimen; (iii) the need for a sufficient treatment duration to potentially impact both acute (hematoma expansion, perihematomal edema) and subacute (inflammation, apoptosis) pathophysiological processes after ICH, and to support intensive rehabilitation.

The 6-h treatment window was selected based on the temporal profile of hematoma expansion in primary ICH, balancing (i) practical feasibility of patient identification, consent, and randomization; (ii) opportunity to affect hematoma expansion, which is the key determinant of functional outcome; (iii) 4- to 6-h therapeutic window for traumatic brain injury; and (iv) 8-h time window in the cerebrolysin thrombectomy trials.

The marketed product cerebrolysin 215.2 mg/mL solution for injection and infusion will be used as the study drug. For details and preparation instructions, please refer to the cerebrolysin Summary of Product Characteristics and package leaflet approved by the President of the Office for Registration of Medicinal Products, Medical Devices and Biocidal Products in Poland.

The cerebrolysin solution should not be mixed with amino acid solutions in one infusion. Vitamins and cardiovascular drugs may be administered simultaneously; however, they should not be mixed with a cerebrolysin solution in one infusion bag.

All subjects will receive care in the stroke unit and will receive stroke treatment and diagnosis according to Polish and international guidelines.

There are six time points of assessment (Table 2).

**Table 2 tab2:** Time points of assessment.

Time range	Assessment point
t0	Stroke onset
Day 1	≤5,5 h after t0: Baseline assessment prior to enrollment and randomization
Day 1	≤ 6 h after t0: Randomization followed by first dose of cerebrolysin (dosing in treatment arm only)
Day 2	24 ± 4 h from randomization
Day 7	7 days ±12 h from randomization
Day 14	14 days ±1 day from randomization
Day 30	30 days ± 2 days from Day 1
Day 90	90 days ± 7 days from Day 1

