At baseline, brain non-contrast computed tomography (NCCT) and computed tomography angiography (CTA) scans, demographics, medical history, physical examination, vital signs, clinical scores [NIHSS, premorbid mRS and Barthel index (BI)], and eligibility criteria review will be recorded. The ICF signature will be collected prior to any study-specific procedure. Procedures completed as part of the standard of care but prior to ICF signature may be used for eligibility verification and baseline assessments.

All subjects, regardless of arm assignment, will have laboratory tests collected, and stroke treatment and rehabilitation programs will be implemented at the investigators’ discretion. Throughout the study, concomitant medications and adverse events (AEs) will be collected. Results will be investigator-assessed using Common Terminology Criteria for Adverse Events (CTCAE) version 5.0 (published November 27th, 2017).

Eight-eight subjects will be enrolled at 1:1 ratio.

After randomization, 44 subjects will receive an intravenous infusion of 50 mL cerebrolysin mixed with 250 mL of saline over 30 min once daily from Day 1 to Day 14 (14 consecutive days of treatment) plus standard of care treatment at the discretion of the investigator (treatment arm). The first dose of cerebrolysin must be administered as soon as possible and within 6 h from ICH onset. Another 44 subjects will be subject to receive standard of care treatment alone at the discretion of the investigator (control arm).

All subjects will be scheduled for intensive motor and/or speech and language rehabilitation, as stated in Polish reimbursement guidelines (120 min Per patient in patients with BI≥75 and 180 min Per patient in those with BI<75 day 5 days a week; additionally, all patients undergo 60 min Rehabilitation on Saturdays; in aphasic patients, speech therapy is additionally applied 5 days a week for 30 min).

Cerebrolysin will be administered once daily from Day 1 to Day 14 or until the end of treatment due to death, intolerable adverse events, subject loss to follow-up, consent withdrawal or study termination. Patients who discontinue treatment and receive at least one dose of cerebrolysin will be asked to attend all follow-up visits. A subject is considered as lost to follow-up when all follow-up efforts have been unsuccessful.

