### Statistical analysis

The study will be analyzed according to the intention-to-treat (ITT) principle. The primary analysis will include all randomized patients regardless of protocol adherence. A secondary per-protocol analysis will include only patients who received at least 80% of the planned cerebrolysin doses in the treatment arm and completed all required assessments.

If the patient’s treatment allocation was disclosed to the outcome adjudicator prior to the assessment, a substitute independent adjudicator will evaluate the patient. Safety analysis will apply to subjects who received at least one dose of cerebrolysin.

Details of the statistical analyses will be provided in the study’s statistical analysis plan (SAP), which will be finalized before enrolling the first patient. Any changes to the methods described in the plan will be described and justified in the final clinical study report.

Data will be summarized using descriptive statistics with 95% confidence intervals (CIs) where applicable. For continuous variables, the number of subjects, mean, standard deviation, median, minimum, and maximum values will be reported. Frequencies and percentages will be used to summarize categorical variables. Results will be presented as proportions or adjusted odds ratios with 95% confidence intervals and corresponding *p*-values. Analyses will be adjusted for the stratification factors (baseline ICH volume and GCS score). Missing data will be handled using multiple imputation methods for the primary and key secondary endpoints, with sensitivity analyses performed using alternative approaches (last observation carried forward, worst-case imputation) to assess the robustness of findings. A tipping-point analysis will be conducted for the primary endpoint to determine the impact of missing data on the final conclusions.

The following subgroup analyses are pre-specified according to age (≤65 vs. >65 years), baseline ICH volume (30–50 mL vs. 51–80 mL), the time from symptom onset to treatment (≤3 vs. >3–6 h), baseline GCS score (8–12 vs. 13–15).

All AEs and SAEs will be summarized, including the number of events, number of subjects, and percentage of subjects reporting these events, tabulated by preferred term from MedDRA Dictionary. Events will also be summarized by severity and by relationship to the study drug.

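### Hematoma size shift: adjusting for two scan times known before allocation would sharpen the estimate; growth before the first dose weakens the binary and relative effect but does not bias the mean difference in mL

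*Protocol article*

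**What the plan says.** Two hematoma endpoints stand under Secondary objectives. The first is binary: "Avoiding hematoma growth from Day 1 to Day 2", with growth defined by an absolute increase above 12.5 mL and a relative increase above 35%. The second is "Absolute hematoma size shift", listed without dates and taken here to cover the same interval.

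Three statements fix the timing:

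- Table 2 (Intervention) puts the baseline work at "≤5,5 h after t0: Baseline assessment prior to enrollment and randomization". Randomisation and the first dose follow, up to 6 h after onset.
- The Intervention section also allows earlier scans: "Procedures completed as part of the standard of care but prior to ICF signature may be used for eligibility verification and baseline assessments". It sets no maximum interval from CT to dose.
- The Day 2 CT falls 24 ± 4 h from randomisation, so it is tied to randomisation and not to the baseline CT.

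On why timing matters, the Introduction states that "hematoma growth occurs mainly within 6 h of symptom onset", and the 6-h window is justified in part by the "opportunity to affect hematoma expansion, which is the key determinant of functional outcome". On the model, Statistical analysis says: "Analyses will be adjusted for the stratification factors (baseline ICH volume and GCS score"). Onset-to-treatment time (≤3 vs >3–6 h) appears there as a subgroup, not as a covariate. Further detail is left to a SAP that is not shown.

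**The concern.** The baseline scan necessarily precedes the first dose, and the gap falls in the hours when, by the article's own account, most growth happens. The drug cannot affect growth in that gap, yet it is scored in both arms.

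Patients also differ in how long after onset they are scanned and how long they then wait. A patient scanned early has more growth still to come than one scanned late, so timing is a source of outcome variation that is known before allocation. The adjustment set named in the article does not use it.

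An effect on hematoma growth is part of the stated study objective, so avoidable loss of sensitivity on these endpoints makes a null result harder to read.

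**Working it through.** **The plan's own figure.** N = 88 rests on survival. At 57.8% vs 27.8% (or 59.4% vs 29.4%), two-sided alpha 0.05 and power 0.80, the pooled two-proportion formula without continuity correction gives 42 per arm, as stated; 84 × 1.05 = 88.2. It reproduces but has no bearing here, because no rate, effect or power is given for hematoma growth. Every growth input below is an assumption.

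**1. Length of the intervals.** The gap from CT to dose can run from minutes to just under 6 h. With randomisation close to dosing, the scan-to-scan interval runs from about 20 h (24 − 4) to just under 34 h (6 + 28).

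**2. Binary endpoint.** Let p be the control growth rate, f the share of control growth events already present before the dose, and r the drug's risk ratio on later events. The treated rate is p·f + p·(1 − f)·r, so the observed risk ratio is f + (1 − f)·r. With p = 25%, r = 0.5 and f = 20%, the treated rate is 5% + 20% × 0.5 = 15%, and the observed risk ratio is 15/25 = 0.60. At 44 per arm:

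| f | observed risk ratio | power, p = 25% |
|---|---|---|
| 0% | 0.50 | 32% |
| 10% | 0.55 | 26% |
| 20% | 0.60 | 21% |
| 30% | 0.65 | 17% |
| 40% | 0.70 | 14% |

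At p = 15%, power goes from 20% to 9% over the same range of f; at p = 35%, from 46% to 19%.

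**3. Relative reduction in volume.** Assume growth decays exponentially after onset with time constant τ, and 0.5–2 h pass from CT to dose. The mean share of later growth that falls before the dose is 45%, 33% and 26% for τ = 2, 3 and 4 h. A drug that halves post-dose growth then appears to cut measured growth by 0.5 × (1 − 0.45) = 27.5%, 0.5 × 0.67 = 33.5% and 0.5 × 0.74 = 37%.

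**4. Mean difference in mL.** Write the change as pre + post + error in control and pre + 0.5·post + error in treated patients. Randomisation makes the expected pre term equal in both arms, so it cancels and the difference is 0.5·E(post). A simulation in which 40% of patients grow confirms this:

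| τ | mean difference, pre-dose growth included or not | control SD with pre-dose growth | control SD without |
|---|---|---|---|
| 2 h | 0.80 mL | 7.2 mL | 4.8 mL |
| 4 h | 1.99 mL | 11.4 mL | 8.7 mL |
| 8 h | 3.11 mL | 14.6 mL | 12.5 mL |

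The difference does not move; only the spread rises.

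**5. What timing covariates recover.** Simulate 88 patients with CT at 0.5–4.5 h after onset, 0.5–2 h to dose (capped at 6 h from onset), τ of 2–4 h, gamma-distributed growth with coefficient of variation 0.7–1.5, 3 mL measurement error, and a drug that halves post-dose growth. Compare models with and without onset-to-CT time and the CT-to-treatment-start interval. The variance ratio of the treatment effect is 0.73 to about 1.0, and power changes by 0 to about +9 points. For example, at τ = 3 h and coefficient of variation 0.7, power goes from 54% to 61%. The gain is largest when growth is early and similar between patients. In the step 4 setting, where 60% of patients do not grow, linear timing terms explain only about 4.7%, 1.8% and 0.5% of the variance for τ = 2, 4 and 8 h.

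**The case against.** The strongest reply is that this is SAP detail. The article gives one general sentence on adjustment, does not say that no other covariate will be used, and defers the rest. That stands in part: the missing covariate cannot be called an error, and the SAP may already contain it. But the article does fix the endpoint window, the baseline-scan rule, the anchor of the Day 2 CT and the stratification factors as the adjustment set, so the suggestion addresses something it states.

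Timing is also partly controlled: baseline is capped at 5.5 h, dosing at 6 h, and onset-to-treatment time is a subgroup. A subgroup split does not adjust the main estimate, however, and control patients have no dose time, so the time must run to randomisation.

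It is also fair that the gain may be close to nil, and that power for the binary endpoint is only 20–46% in the risk-ratio-0.5 scenarios even with no pre-dose growth. A null result there would be hard to read in any case.

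A reader might infer that any drug effect is diluted or that the comparison is biased. The documents do not support that. Under an additive model the mean mL difference is unchanged, and randomisation balances scan timing in expectation. Nor would a rule to use the last pre-randomisation scan help: no repeat scan is scheduled, and such a rule could separate the baseline volume from the volume used for stratification.

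**Conclusion.** The point holds as a matter of precision. Growth before the first dose counts in both arms. It attenuates the binary and relative effect by an amount that the documents do not allow anyone to fix, and it adds variance to the absolute size shift without biasing the mean difference. Scan timing should be prognostic by the article's own account and is absent from the named adjustment set. Using it would cut the variance of the size-shift effect by about 0–27% and change power by 0 to +9 points. Those ranges rest on assumed exponential decay, assumed scan and dosing delays, and assumed between-patient variation; if many patients do not grow, almost nothing is gained. No covariate can take pre-dose growth out of the outcome. This is a minor improvement to a secondary endpoint of a pilot for which no power is claimed.

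**What to change.** In the analysis of absolute hematoma size shift, add two continuous covariates alongside the stratification factors: time from onset (or last known well) to the baseline CT, and the interval from the baseline CT to randomisation. Both are known before allocation and exist in both arms. If growth events are few, keep the binary growth model with the strata only.

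The cost is a line in the SAP and the clock times of onset, baseline CT and randomisation. The downside is two more model terms in 88 patients. No extra scan, visit or change of treatment is involved.

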### Data collection, management, and monitoring

Study data will be collected as part of routine medical care. All data will be anonymized and reported using a CRF maintained by the sponsor. The investigator must ensure that data is entered into the CRF as soon as possible after the study visit.

Entries and corrections to the CRF data can be made by the investigator or delegated staff. Correction must include, at minimum, the original and corrected/changed data, identification of the person correcting/changing the data, and date and time of the correction/change.

Medical history and AEs will be coded using MedDRA Dictionary. Concomitant medication will be coded using the WHO Drug Dictionary.

In accordance with the ICH GCP principles, the sponsor will arrange study monitoring. Monitoring visits will be made at appropriate times to ensure that the trial is conducted and documented properly in compliance with the protocol, ICH GCP, and applicable local regulations. The sponsor designee (Clinical Research Associate, CRA) will review source documents to verify consistency with the CRF data (source data verification). The CRA will also provide information and support to the investigational sites. These activities will ensure data are attributable, legible, contemporaneous, original, and accurate.

Source data are defined as information in original records and certified copies of original records of clinical findings, observations, data, or other activities in a clinical study necessary for study reconstruction and evaluation.

### Statistical analysis

The study will be analyzed according to the intention-to-treat (ITT) principle. The primary analysis will include all randomized patients regardless of protocol adherence. A secondary per-protocol analysis will include only patients who received at least 80% of the planned cerebrolysin doses in the treatment arm and completed all required assessments.

If the patient’s treatment allocation was disclosed to the outcome adjudicator prior to the assessment, a substitute independent adjudicator will evaluate the patient. Safety analysis will apply to subjects who received at least one dose of cerebrolysin.

Details of the statistical analyses will be provided in the study’s statistical analysis plan (SAP), which will be finalized before enrolling the first patient. Any changes to the methods described in the plan will be described and justified in the final clinical study report.

Data will be summarized using descriptive statistics with 95% confidence intervals (CIs) where applicable. For continuous variables, the number of subjects, mean, standard deviation, median, minimum, and maximum values will be reported. Frequencies and percentages will be used to summarize categorical variables. Results will be presented as proportions or adjusted odds ratios with 95% confidence intervals and corresponding *p*-values. Analyses will be adjusted for the stratification factors (baseline ICH volume and GCS score). Missing data will be handled using multiple imputation methods for the primary and key secondary endpoints, with sensitivity analyses performed using alternative approaches (last observation carried forward, worst-case imputation) to assess the robustness of findings. A tipping-point analysis will be conducted for the primary endpoint to determine the impact of missing data on the final conclusions.

The following subgroup analyses are pre-specified according to age (≤65 vs. >65 years), baseline ICH volume (30–50 mL vs. 51–80 mL), the time from symptom onset to treatment (≤3 vs. >3–6 h), baseline GCS score (8–12 vs. 13–15).

All AEs and SAEs will be summarized, including the number of events, number of subjects, and percentage of subjects reporting these events, tabulated by preferred term from MedDRA Dictionary. Events will also be summarized by severity and by relationship to the study drug.

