All subjects will undergo neurological assessments conducted by experienced stroke neurologists designated by the investigator: National Institutes of Health Stroke Scale (NIHSS) on Day 1 (at baseline), Day 2, Day 7, Day 14, Day 30, and Day 90; modified Rankin Scale (mRS) and BI on Day 1 (premorbid), Day 30 and Day 90.

The baseline brain NCCT and CTA will be completed on Day 1 (baseline) and the follow-up CT scan on Day 2 (24 ± 4 h from randomization) and day 14 ± 1 right after treatment termination. This will allow to assess the evolution of swelling which also reflects the status of blood–brain barrier permeability. The magnetic resonance imaging (MRI) scan will be completed on Day 90 ± 7 (41).

If on-site neurological assessment is not possible, investigators should schedule a telephone visit and collect information remotely.

Please refer to Table 3 for study schedule details. The trial assessment flowchart is presented in Figure 1.

**Table 3 tab3:** Treatment schedule.

Treatment/procedure	Day 1 (screening)	Day 1 (baseline)	Day 2	Day 7	Day 14	Day 30	Day 90
Informed consent	x						
Eligibility assessment	x						
Demographics	x						
Medical history	x						
Physical examination*	x					x	x
ECOG score	x					x	x
Vital signs**	x					x	x
Pregnancy test, if applicable	x						
CT scan***	x		x		x		
MRI scan							x
mRS		x				x	x
NIHSS		x	x	x	x	x	x
Barthel index		x				x	x
Adverse events	x	x	x	x	x	x	
Concomitant medications	x	x	x	x	x	x	x
Randomization		x					
Cerebrolysin treatment (if allocated)		x	x	x	x		

*Physical examination: assessment of general appearance and review of organ systems (dermatologic, head, eyes, ears, nose, mouth/throat/neck, thyroid, lymph nodes, respiratory, cardiovascular, gastrointestinal, extremities, musculoskeletal, and neurologic systems). **Vital signs: pulse rate, respiratory rate, O2 saturation, body temperature, and blood pressure (systolic/diastolic, subjects should be supine/sitting for 5 min before assessment). ***Baseline brain NCCT and CTA scan on Day 1 (baseline) and follow-up CT scan on Day 2 (24 ± 4 h from randomization), and Day 14 (±1 day from randomization).

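### The secondary per-protocol set conditions on survival: its dose rule excludes early deaths in the cerebrolysin arm only

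*Protocol article*

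**What the plan says.** Under Statistical analysis, the protocol article sets two analysis populations for the comparison of arms. The primary one is intention-to-treat: "The primary analysis will include all randomized patients regardless of protocol adherence". The secondary per-protocol set keeps "only patients who received at least 80% of the planned cerebrolysin doses in the treatment arm and completed all required assessments".

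The Intervention section supplies what is needed to apply that rule. Cerebrolysin is given on 14 consecutive days, and continues "until the end of treatment due to death, intolerable adverse events, subject loss to follow-up, consent withdrawal or study termination". Assessments extend well past dosing: NIHSS is scheduled to Day 90, and the functional scales are taken as "modified Rankin Scale (mRS) and BI on Day 1 (premorbid), Day 30 and Day 90". Mortality and mRS 0–2, both at Day 90, are the primary outcomes. The per-protocol definition makes no exception for patients who die.

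**The concern.** Both per-protocol conditions can fail simply because the patient died. The dose condition counts doses planned, not doses due while alive, and it can bind only in the arm that receives doses. Early deaths then leave the cerebrolysin arm and stay in the control arm. In a trial where death is a primary outcome and the sample size rests on a survival difference, that selection is on the outcome itself and always favours cerebrolysin.

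The per-protocol analysis is the only adherence-based comparison the article names, and results are to be shown with p-values. The article also says that early efficacy signals would justify a larger trial. A per-protocol survival advantage produced by the definition could be taken for such a signal.

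**Working it through.** **Dose threshold.** 0.80 × 14 = 11.2, so at least 12 doses are needed. A treated patient who dies before dose 12 cannot qualify.

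**Arm size.** The plan's 42 per arm reproduces for 60% vs 30% survival (two-sided 5%, 80% power, pooled variance): n = [1.96·√(2 × 0.45 × 0.55) + 0.8416·√(0.24 + 0.21)]² / 0.30² = (1.379 + 0.565)² / 0.09 ≈ 42. With the allowance for loss the plan enrols 44 per arm, which is used below.

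**Reading 1: the dose rule alone.** Let m be Day 90 mortality in both arms (no drug effect), s the share of deaths before dose 12, and g the share of survivors at mRS 0–2. Then:

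- per-protocol mortality, cerebrolysin: (m − ms) / (1 − ms); control: m
- per-protocol mRS 0–2, cerebrolysin: (1 − m)g / (1 − ms); control: (1 − m)g

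The documents give none of m, s or g for this population. They are assumed: m 20–50%, s 30–70%, g 40%. For m = 0.40 and s = 0.50, mortality is (0.40 − 0.20)/(1 − 0.20) = 25.0% against 40%, and mRS 0–2 is 0.24/0.80 = 30.0% against 24.0%.

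False benefit is the share of 200,000 simulated trials per scenario in which a pooled two-sided 5% z-test is significant in favour of cerebrolysin (nominal 2.5%).

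| m | s | Treated patients excluded (expected, 44ms) | Mortality, cerebrolysin vs control | False benefit, mortality | mRS 0–2, cerebrolysin vs control | False benefit, mRS 0–2 |
|---|---|---|---|---|---|---|
| 20% | 30% | 2.6 | 14.9% vs 20% | 9% | 34.0% vs 32.0% | 4% |
| 30% | 50% | 6.6 | 17.6% vs 30% | 25% | 32.9% vs 28.0% | 7% |
| 40% | 50% | 8.8 | 25.0% vs 40% | 29% | 30.0% vs 24.0% | 9% |
| 40% | 60% | 10.6 | 21.1% vs 40% | 43% | 31.6% vs 24.0% | 12% |
| 50% | 70% | 15.4 | 23.1% vs 50% | 65% | 30.8% vs 20.0% | 19% |

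The first and last rows are the extremes of the assumed range. With all deaths kept and counted as failures, the rate is about 2–3% for both outcomes.

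**Reading 2: the assessment condition also applies, in both arms, to Day 90.** Every death by Day 90 is removed and per-protocol mortality is 0% against 0%. Expected patients remaining: 88 × 0.70 = 61.6 at 30% mortality and 88 × 0.60 = 52.8 at 40%. For an ineffective drug the false-benefit rate on mRS 0–2 is about 2.6%, so there is no inflation. A drug that changes who survives can still be flattered. Suppose mortality is 40% on cerebrolysin and 30% on control, with the extra deaths all among patients who would have been mRS 3–5. Intention-to-treat mRS 0–2 is 28% in both arms. Per-protocol it is 0.28/0.60 = 46.7% against 0.28/0.70 = 40.0%, so a harmful drug looks better.

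**Reading 3: the assessment condition applies to the treatment arm only.** The sentence permits this too. Every treated death is then removed and every control death kept. At 30% mortality, per-protocol mortality is 0% against 30%, and mRS 0–2 is 40% against 28%.

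**The case against.** The strongest reply is that the per-protocol analysis is declared secondary, the trial is a pilot, and the primary analysis keeps everyone randomized. That stands, and it limits the severity.

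The large figures also depend on the reading. They need control deaths to stay in. If the assessment condition removes deaths in both arms, the mortality comparison is empty and an ineffective drug gains nothing. The two results cannot both occur, and the article does not say which applies. It could even intend only the assessments due while alive, which would leave the dose-rule problem in place. Further, the highest rates are for mortality, which is labelled the safety outcome, and the article never says that per-protocol mortality will be tested. For mRS 0–2 the inflation is much smaller. The mortality level and the share of early deaths are assumptions. The 6-month survival quoted for planning comes from another ICH population, with volumes up to 25 mL against 30–80 mL here. All of this stands, and it is why ranges are given.

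A reader might go further, since "Missing data will be handled using multiple imputation methods for the primary and key secondary endpoints" carries no stated exception for death, and infer that NIHSS and Barthel scores will be invented for dead patients or that deaths vanish from the secondary endpoints generally. The document does not support this. It never says that a score absent through death counts as missing, does not identify which secondary endpoints are key, and leaves details to an analysis plan that is not shown. A known death needs no imputation for mortality or for mRS 0–2. Nothing removes deaths from the intention-to-treat secondary analyses.

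None of this rescues the dose rule. It is stated in the article, and an analysis plan consistent with it would inherit the defect.

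**Conclusion.** The point holds for the secondary per-protocol analysis only, and should be fixed. As written, the set conditions on survival, and its dose condition does so in one arm.

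Under the dose rule alone, an ineffective drug would show a nominally significant benefit in about 9–65% of trials for mortality and about 4–19% for mRS 0–2, against 2.5%. These rates rest on 44 per arm, assumed mortality of 20–50%, an assumed 30–70% of deaths before dose 12, and 40% of survivors independent. If the assessment condition removes deaths in both arms, there is no inflation for an ineffective drug, but per-protocol mortality is uninformative and a drug that alters survival can be misjudged. Neither reading, nor one limiting the assessment condition to the treatment arm, gives a sound per-protocol mortality comparison.

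The intention-to-treat primary analysis and the sample size are unaffected. How death is scored on NIHSS and the Barthel Index is a matter for the analysis plan and is not counted as a fault here.

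**What to change.** Redefine the per-protocol set so that nobody leaves it because of death:

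- For the cerebrolysin arm, define adherence as at least 80% of the doses due up to death or Day 14, whichever comes first.
- Count death as a completed outcome: a death for mortality, a failure for mRS 0–2.
- Replace the requirement for all assessments with vital status or mRS at Day 90.
- State that the assessment condition applies identically to both arms.

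The cost is wording only. The set becomes slightly less restrictive, and the sample size stays at 88. The analysis will still select on adherence after randomization, so it should remain supportive of the intention-to-treat result.
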